## Abstract

**Background:**

As the availability and performance of artificial intelligence (AI)–based clinical decision support (CDS) systems improve, physicians and other care providers poised to be on the front lines will be increasingly tasked with using these tools in patient care and incorporating their outputs into clinical decision-making processes. Vignette studies provide a means to explore emerging hypotheses regarding how context-specific factors, such as clinical risk, the amount of information provided about the AI, and the AI result, may impact physician acceptance and use of AI-based CDS tools. To best anticipate how such factors influence the decision-making of frontline physicians in clinical scenarios involving AI decision-support tools, hypothesis-driven research is needed that enables scenario testing before the implementation and deployment of these tools.

**Objective:**

This study’s objectives are to (1) design an original, web-based vignette-based survey that features hypothetical scenarios based on emerging or real-world applications of AI-based CDS systems that will vary systematically by features related to clinical risk, the amount of information provided about the AI, and the AI result; and (2) test and determine causal effects of specific factors on the judgments and perceptions salient to physicians’ clinical decision-making.

**Methods:**

US-based physicians with specialties in family or internal medicine will be recruited through email and mail (target n=420). Through a web-based survey, participants will be randomized to a 3-part “sequential multiple assignment randomization trial (SMART) vignette” detailing a hypothetical clinical scenario involving an AI decision support tool. The SMART vignette design is similar to the SMART design but adapted to a survey design. Each respondent will be randomly assigned to 1 of the possible vignette variations of the factors we are testing at each stage, which include the level of clinical risk, the amount of information provided about the AI, and the certainty of the AI output. Respondents will be given questions regarding their hypothetical decision-making in response to the hypothetical scenarios.

**Results:**

The study is currently in progress and data collection is anticipated to be completed in 2024.

**Conclusions:**

The web-based vignette study will provide information on how contextual factors such as clinical risk, the amount of information provided about an AI tool, and the AI result influence physicians’ reactions to hypothetical scenarios that are based on emerging applications of AI in frontline health care settings. Our newly proposed “SMART vignette” design offers several benefits not afforded by the extensively used traditional vignette design, due to the 2 aforementioned features. These advantages are (1) increased validity of analyses targeted at understanding the impact of a factor on the decision outcome, given previous outcomes and other contextual factors; and (2) balanced sample sizes across groups. This study will generate a better understanding of physician decision-making within this context.

**International Registered Report Identifier (IRRID):**

DERR1-10.2196/54787

## Introduction

The implementation of artificial intelligence (AI) in health care is recognized as a promising means to advance medicine by providing timelier diagnoses, reducing administrative burden, and predicting outcomes with higher accuracy. As the availability and performance of AI-based clinical decision support (CDS) systems improve, physicians and other care providers poised to be on the front lines will be increasingly tasked with using these tools in patient care and incorporating their outputs into clinical decision-making processes. Due to the few instances of CDS systems in current use by frontline physicians, there is limited empirical research studying how these tools and the specific characteristics of these tools influence physicians’ engagement with AI and their clinical decision-making.

Previous research has identified factors that may influence physicians’ use and decision-making in the context of AI-based CDS systems, including clinical risk, explainability, as well as trust and transparency [1,2]. While the role of trust and transparency in clinician acceptance has been emphasized in the literature in recent years, findings supporting the claim that transparency about AI can actually support clinical decision-making are mixed [3-5]. Jussupow et al [6] used vignette-based experiments with physicians to understand how AI influences their decision-making, finding that the timing of the presentation of the AI result, whether or not the AI result aligns with the physician’s opinion, and the experience level of the physician may all be factors that influence the decision-making of a physician who is tasked with incorporating an AI-based CDS system in their diagnostic care. Such knowledge is critical to ensuring successful implementation of AI in health care, but due to the many differences in the types of applications of AI, subspecialties, and health care systems, there is a high degree of heterogeneity in physician attitudes regarding acceptance, and factors influential to their decision-making are likely to be context specific.

Experimental vignette studies such as Jussupow et al [6] provide an effective means to explore emerging hypotheses regarding how context-specific factors may impact physician acceptance and use of AI-based CDS tools or to generate new hypotheses regarding how individuals may react to specific scenarios involving new applications where much is unknown. Vignettes are narrative representations of real-world scenarios, providing context-specific stimuli and characteristics with which respondents may practice decision-making without actual exposure to such scenarios [7-9]. Experimental vignette studies have been used to understand reactions toward algorithmic errors [10], physician liability while using AI [11], and physician diagnostic accuracy in the context of AI [12].

In this study, we use a novel vignette survey design—“sequential multiple assignment randomization trial (SMART) vignettes,” proposed by [name] and [name] (unpublished data)—which uses the SMART design developed by Murphy [13] in a web-based vignette survey. The novelty of this survey design is that it features 2 design elements previously not seen in conventional designs: sequential randomization and adaptive allocation. In experimental vignette studies, hypothetical characteristics (factors) are varied according to levels. Each respondent is randomly assigned to 1 vignette characterized by a specific realization of each factor in order to test how the factors influence responses. In conventional vignette studies, this randomization typically occurs once before the study is administered at baseline, followed by a complete set of questions. Sequential randomization, on the other hand, involves randomly assigning respondents to vignettes multiple times throughout the survey, with each randomization point followed by a subset of questions pertaining to the factor being tested. This latter approach allows inferences about the final response based on previous factors and responses. In contrast, baseline randomization in traditional designs is limited to inferences on how likely each combination of responses is based on given factors. Adaptive allocation is a way to adjust randomization probabilities to encourage more balanced groups for such inference. While these 2 concepts are not novel in and of themselves—the former appears in the field of SMARTs [13,14] and the latter is from Efron [15]—the application of such concepts in the context of vignette survey methodology is novel, to the best of our knowledge.

To best anticipate the decision-making of frontline physicians in scenarios involving AI CDS tools, a hypothesis-driven approach that enables scenario testing in advance of clinical implementation of these tools is urgently needed. As such, we propose to undertake an empirical study engaging frontline physicians in order to better understand the causal effects of specific contextual and algorithmic features on their clinical judgments and perspectives. For our approach, we will conduct a “SMART vignette” web-based survey that features hypothetical scenarios based on emerging or real-world applications of AI-based CDS systems. These scenarios will vary systematically by features related to clinical risk, the amount of information provided about the AI, and the AI result in order to test and determine the causal effects of specific factors on the judgments and perceptions salient to physicians’ clinical decision-making.

## Methods

### Overview

The purpose of this study is to better understand the impact of algorithm-related features on physician acceptance and attitudes related to clinical decision-making in the context of AI CDS tools. US-based physicians with specialties in the family or internal medicine (ie, those most poised to be on the “front lines” of nonemergency patient care) who are listed in the most recent version of the American Medical Association (AMA) Physician Masterfile (PMF) will be recruited through email and mail (target n=420). Through a web-based survey, participants will respond to baseline questionnaires regarding their demographics, professional experience, and attitudes toward and experience with AI or machine learning (ML) in medicine. They will then be randomly assigned to a 3-part “SMART vignette” detailing a hypothetical clinical scenario involving an AI decision support tool. Each respondent will progress through the multistage vignette survey, and at each stage, they will be randomly assigned to one of the possible vignette variations. The 3 randomization points will vary in regard to the level of clinical risk (higher risk vs lower risk), the amount of information provided about the AI (more information vs less information), and the certainty of the AI output (higher certainty vs lower certainty). After each randomization point, participants will be asked to respond to questions regarding their hypothetical decision-making as it relates to these factors.

This study is part of a broader project studying stakeholder views regarding the development and use of AI and ML in medicine (National Center for Advancing Translational Sciences R01-TR-003505). It is built upon findings from the first phase of the broader project, in which AI and ML researchers and physicians were interviewed regarding ethical considerations they have encountered or anticipated in the development, refinement, and application of AI and ML in medicine [16,17]. Insights from this phase of research were used to create hypothetical but realistic scenarios for this study and to inform the development of questions assessing physician decision-making in these scenarios.

### Recruitment

US-based physicians who are listed in the most recent version of the AMA PMF as specializing in family medicine or internal medicine will be eligible to participate in this study. The PMF is a comprehensive database of US physicians used for verifying professional credentials. Through the AMA-approved third-party vendor Medical Marketing Services, Inc, we will obtain the email and mailing addresses of a sampling frame of 10,000 physicians who meet our inclusion criteria. Physicians who are identified in this sampling frame will be contacted with invitations to participate in our web-based survey.

Through the third-party vendor Medical Marketing Services, Inc, we will send up to 4 email invitations to each physician in the sampling frame. Each email will provide a short description of our study and a web link to the web-based survey. Based on previous studies of this method of recruitment, we anticipate a 1.5% response rate [18]. If the target recruitment goal of 420 is not reached after 4 email invitations are sent, we will send a follow-up invitation by mail to any physicians in the original sampling frame who have not yet responded to the survey. Each mailed invitation will briefly describe our study and will contain a web address for the web-based survey.

### Ethical Considerations

This project has received human participant research ethics approval from the Stanford University Institutional Review Board (65168). Upon navigating to the web-based survey, potential participants will be presented with a web-based informed consent form that details the content of the survey and the anticipated risks and benefits of participation. Participants will only proceed to the web-based vignette survey if they provide consent. Participation will be voluntary, and all responses will be anonymous. All participants will be compensated for their time and effort with a US $10 Amazon gift code at the completion of the survey.

### Hypotheses and Outcome Variables

Our hypotheses are the following:

Hypothesis 1: higher degrees of clinical risk associated with the algorithm will influence lower levels of physician agreement with the effectiveness of and confidence in using the algorithm to help guide treatment decisions.Hypothesis 2: disclosure of details of the algorithm will impact physicians’ attitudes of confidence and efficacy, depending on their previous exposure to AI (ie, education, training, and clinical experience). We hypothesize that greater disclosure will influence positive attitudes among physicians with greater exposure but will have a negative or no impact on physicians with less exposure.

The primary outcome variables will be physicians’ ratings, on a Likert scale, of perceived confidence in the AI algorithm in helping the physician make the best treatment recommendation for their patient (eg, “The AI result improved the confidence I have in my final decision”; from 1=“strongly disagree” to 5=“strongly agree”), as well as the perceived effectiveness of the use of the AI algorithm (eg, “Overall, the AI improved the care that I was able to provide to the patient”; rated on a 5-point scale from 1=“strongly disagree” to 5=“strongly agree”).

### Survey Design

#### Survey Instruments

Demographic characteristics (age, gender, educational level, race, and ethnicity) and professional characteristics (specialty type and years of experience) will be assessed through a baseline demographics questionnaire (13 questions). Experience with and attitudes toward AI and ML applications in medicine will be assessed using adapted measures (7-10 questions assessing experience and 11 questions assessing attitudes) [19,20]. A 3-part sequentially randomized vignette detailing a clinical scenario involving a CDS system will be presented to each participant; follow-up questions will assess participant attitudes and decision-making in the context of the vignette scenario (21 questions).

#### Vignette Development and Design

The vignettes used in this study were developed based on scenarios encountered by researchers and clinicians, as told in interviews in the first phase of this project [16]. Based on these findings, the dimensions in which the vignettes are systematically varied include the context of the decision-making scenario (higher risk vs lower risk), the amount of information provided regarding the algorithm (more information vs less information), and the certainty of the AI output (higher certainty vs lower certainty). The full content of the vignettes is available in Multimedia Appendix 1.

#### SMART Design

We have harnessed a design element that originates from clinical trial design: SMART [13,21,22]. [name] and [name] (unpublished data) report the design. First, we use randomization probabilities to assign the subsequent vignette, which allows for tailoring the sequence of assigned vignettes to the individual instead of predetermined assignments of combinations of vignettes. The web-based survey format is particularly amenable to the design in which the subsequent questions are randomized. To the best of our knowledge, the SMART design has not yet been applied in the area of survey designs. SMART designs have been used in the evaluation of treatment algorithms for several psychiatric disorders (eg, depression in the Sequenced Treatment Alternatives to Relieve Depression and Clinical Antipsychotic Trials of Intervention Effectiveness studies) and for the treatment of advanced prostate cancer [23,24].

As shown by Figure 1 (adapted from [name] and [name]—unpublished data), we configured our SMART vignette to have 3 dimensions, each with 2 levels: patient risk (higher risk vs lower risk), information on AI (more information vs less information), and certainty of AI output (higher certainty vs lower certainty), respectively. Corresponding vignette scenarios and question sets were input for each combination of randomization sequences. One question from every question set was flagged to serve as a primary question, the response for which was used to adaptively allocate the participants [16,17]. For 5-point Likert scale primary questions, participants who respond from “1” to “3” are assigned to response group 0, while those who respond with “4” to “5” are assigned to response group 1. For yes or no questions, “yes” corresponds to response group 1 and “no” to response group 0. The probability of Efron’s [15] biased coin was prespecified to be 0.667.

**Figure 1 figure1:**
[figure not shown]
Study design for the web-based vignette survey featuring sequential randomization. Yellow boxes indicate a randomization point, blue boxes indicate vignette content, and orange boxes indicate responses. Respondents will be physicians in family medicine or internal medicine across the United States. ADHD: attention-deficit/hyperactivity disorder; AI: artificial intelligence; SSRI: selective serotonin reuptake inhibitors.

### Power Analysis

We performed a sample size estimation for determining the best embedded dynamic treatment regime using the approach outlined in Artman et al [25] for power analysis in a SMART design. Using the R package *smartsizer* (R Foundation for Statistical Computing) that implements Monte Carlo simulations in Artman et al [25], we calculated that the number of individuals needed to enroll in the vignette experiment is 420 to guarantee at least 80% power to detect an effect size of 0.15.

### Survey Implementation

The SMART vignette survey will be administered on the internet using a web application created by our research team and hosted by Stanford University [26]. The application was developed using Python Flask and deployed using Amazon Beanstalk and Elastic File System, with survey responses stored on a secure SQLite database. This platform allows sequential randomization and adaptive allocation, which are features not yet offered by other survey software such as Qualtrics or Research Electronic Data Capture (REDCap; Vanderbilt University).

The study survey went through a round of internal testing before its launch. Dummy responses were created to ensure data were being properly parsed and stored. The research team tested the application on various devices to identify errors and provide feedback on the user experience and user interface. After a few rounds of internal testing, all study responses and parameters were reset for launch.

Unique user IDs were generated for each potential participant. As part of the recruitment emails and letters, participants will be asked to log into the SMART vignette survey using their assigned user ID and a provided study ID. Respondents have the option to exit and return to the survey at any time. Once a respondent has submitted a complete response, a US $10 Amazon gift card code will be claimed and displayed. The study will remain open to responses until the target number of responses is reached.

### Statistical Analysis

Regression models will be used to determine the causal effects of contextual dimensions on clinician judgments, where confidence is an outcome and the assignment indicator, age, gender, and race are variables. We will estimate “conditional vignette effects” on physicians’ judgments (ie, the effect of the vignette context within subgroups defined by strata of the baseline variables).

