To empirically test these factors, this study uses a novel vignette study method, “SMART vignettes,” an adaptation of the SMART design developed by Murphy [13], applied to web-based survey designs. Further details on the methodology can be found in [name] and [name] (unpublished data). This novel method leverages 2 new design characteristics, namely sequential randomization and adaptive allocation. Our newly proposed “SMART vignette” design offers several benefits not afforded by the extensively used traditional vignette design, due to the 2 aforementioned features. These advantages are (1) increased validity of analyses targeted at understanding the impact of a factor on the decision outcome, given previous outcomes and other contextual factors; and (2) balanced sample sizes across groups.

Strengths of the proposed survey include the use of the sequential randomization design feature, which will allow the presentation of vignettes to be tailored to the individual. Our design offers an advantage above a “rule-based, branching logic approach,” the predominant approach used in web-based surveys, in which a particular response determines the subsequent question to be the same across all respondents [28,29], as well as a single-time baseline randomization in conventional vignette studies. The use of sequential randomization in this web-based survey will enable assessments of the causal effects of contextual information in the algorithms on the judgments of physicians entrusted with applying and implementing the use of the algorithms. In addition, the adaptive quality of the survey may allow for a greater sense of interactivity from the perspective of the survey respondent. Potential limitations of this study include a low response rate, as previously documented in the literature regarding physicians, as well as possible response fatigue, as is commonly experienced in survey studies. Another limitation is that the novel design features we presented are not yet widely available on existing survey platforms (eg, REDCap and Qualtrics) and thus may limit the reproducibility of this particular method. This represents an area of future research.

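### Information and certainty assignments are balanced on the previous response group, but the stated model leaves that group out, so tests of those two main effects are likely to be mildly conservative

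*Protocol article*

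**What the plan says.** Three two-level factors are randomised in order: patient risk, information about the AI, certainty of the AI output (protocol article, SMART Design). One primary question per question set is flagged, "the response for which was used to adaptively allocate the participants". On Likert items "participants who respond from “1” to “3” are assigned to response group 0" and higher answers go to group 1; for yes/no items, yes is group 1. The "biased coin was prespecified to be 0.667".

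The Introduction gives the purpose. Of sequential randomisation it says: "This latter approach allows inferences about the final response based on previous factors and responses". Adaptive allocation is there to "adjust randomization probabilities to encourage more balanced groups for such inference". The Discussion lists as the design's first advantage "increased validity of analyses targeted at understanding the impact of a factor on the decision outcome, given previous outcomes and other contextual factors".

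Statistical Analysis takes confidence as an outcome and states that "the assignment indicator, age, gender, and race are variables". Conditional vignette effects are explained there as effects within strata of baseline variables. A response given during the vignette is not a baseline variable, and neither sentence mentions one.

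**The concern.** The variable that drives allocation at stages 2 and 3 is missing from the stated model. When assignment is balanced on something that predicts the outcome, the treatment contrast varies less between repetitions of the study than under simple randomisation. A regression that omits the balancing variable does not see this. It leaves the explained variation in the residual and reports a standard error that is too large, so confidence intervals are too wide and tests reject less often than their nominal level. The precision gained by balancing is then not used.

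The conditional effects as described also stop at baseline strata, although effects given earlier responses are put forward as a reason for using this design. Sample is scarce: Recruitment anticipates a 1.5% response rate, and Results reports 35 complete responses from the email phase against a target of 420.

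**Working it through.** **Inputs.** From the article: N = 420, three sequential two-level factors, coin 0.667, binary response groups, and the model terms in Statistical Analysis. Assumed: how strongly earlier responses predict the later rating, which the article does not give; that the coin balances within combinations of earlier assignments and responses, since its strata are not spelled out; and a continuous rating with SD 1.

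The article gives no standard error to reproduce. Its 420 comes from a regime-selection simulation whose covariance, effect vector and alpha are not printed, so it cannot be rerun. It is used here only as N.

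**Ceiling by formula.** For a 1:1 factor the unadjusted model SE is 2/√420 = 0.0976. If the coin balanced perfectly on responses explaining a share R² of the variance, the true SE would be 2√(1−R²)/√420, so the model SE would be too large by a factor of 1/√(1−R²):

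- R² = 5%: 1/√0.95 = 1.026
- R² = 15%: 1/√0.85 = 1.085
- R² = 30%: 1/√0.70 = 1.195
- R² = 50%: 1/√0.50 = 1.414

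The real coin balances imperfectly, and the information assignment sees only the stage-1 response, so actual ratios should generally be lower.

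**Simulation by variance explained** (3,000 runs, response groups omitted). Cells give model SE / empirical SD, then null rejection at two-sided 5%.

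| R² from earlier responses | Information | Certainty |
|---|---|---|
| 5% | 1.03; 4.5% | 1.01; 4.6% |
| 15% | 1.05; 4.1% | 1.06; 3.9% |
| 30% | 1.09; 2.8% | 1.15; 2.6% |
| 50% | 1.20; 1.5% | 1.29; 1.0% |

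With the preceding response groups in the model, the ratios are 0.98 to 1.01 and rejection is 4.9% to 5.6%. With simple randomisation at R² = 30% and the groups omitted, the ratios are 1.00 and rejection 5.0% to 5.1%. The excess therefore comes from balancing and then ignoring the balancing variable.

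**Simulation by correlation between stage ratings** (1,500 runs). This is a different scale from R² above. Model SE / true SE for the information and certainty main effects is 1.02 to 1.04 at correlation 0.2, 1.06 to 1.08 at 0.4, and 1.13 to 1.17 at 0.6. Rejection is 2% to 3.5% at 0.4 to 0.6 and returns to about 5% after adjustment.

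**Power for the two main effects.** The difference detectable with 80% power at 210 per level is (1.960 + 0.842) × √(2/210) = 0.27 SD. At that difference, power without and with the history terms is:

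| Correlation | Information | Certainty |
|---|---|---|
| 0.4 | 80.8% → 82.9% | 80.1% → 85.6% |
| 0.6 | 81.1% → 87.7% | 81.3% → 91.3% |

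**The stated hypotheses.**

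- Hypothesis 1 (risk, stage 1): no response precedes the assignment. The simulated SE ratio is 0.99 to 1.03, which is no systematic excess.
- Hypothesis 2 (information effect depending on AI exposure): for the interaction, with a binary exposure split 50:50, the unadjusted ratio is 0.98 to 1.01. The coin does not balance within exposure strata, so the SE is correctly sized. Adjustment shrinks it by about 1%, 5% and 12% at correlations 0.2, 0.4 and 0.6.
- The information effect within one exposure subgroup: ratio 1.01 to 1.06 and rejection 4.3% to 4.8% at correlations 0.4 and 0.6.

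**Why adjustment must be stage-specific.** At R² = 30%, adding the response groups to the model for risk moved its estimate from −0.16 to about 0. Those responses come after the risk assignment and carry part of its effect.

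**The case against.** The strongest reply is that little goes wrong for the hypotheses the article states. That stands: Hypothesis 1 is untouched, the interaction for Hypothesis 2 is validly tested without adjustment, and no hypothesis is stated about certainty, where the excess is largest at the higher correlations. Without adjustment, power at 0.27 SD is still 80% to 81%, so the loss is relative to a better model.

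A second reply is that the article is condensed and stage-specific covariates may sit in an analysis plan not shown. This carries some weight, since the section is two sentences long. But it is not silent: it names model terms and defines the conditional effects, and both leave out the allocation variable.

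Three stronger readings are tempting and are not supported:

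- A reader might infer that the three factors are collapsed into one indicator. The noun is singular, but the same sentence speaks of models and dimensions in the plural, so one model per factor is equally possible.
- A reader might infer that the standard errors are too wide throughout, or that the results are biased. The excess concerns two main effects, depends on a correlation the article does not give, and errs on the conservative side.
- A reader might infer that the study has abandoned a promised analysis. The article says that sequential randomisation "allows inferences about the final response based on previous factors and responses"; it does not commit this study to reporting such estimates, and the randomised contrasts remain valid causal comparisons.

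**Conclusion.** The point holds in limited form. Allocation at stages 2 and 3 uses the previous response group; the stated model and conditional effects do not. For the information and certainty main effects, model standard errors are about 2% to 17% too wide and 5% tests reject at about 2% to 5%, if stage ratings correlate at 0.2 to 0.6 and the coin works within assignment-and-response histories. If earlier responses explain only 5% of the variance, the excess is 1% to 3%. There is no bias and no inflated false-positive rate. Hypothesis 1 is unaffected. The interaction for Hypothesis 2 has valid standard errors and would gain only precision. This is a modest loss of efficiency and a mismatch between the design's rationale and its stated analysis, worth correcting because the correction is cheap.

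**What to change.** In Statistical Analysis, name the three factors and specify one model for each:

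- **Risk:** baseline covariates only; no response given after the risk assignment.
- **Information, and its interaction with AI exposure:** add risk arm, stage-1 response group and their product.
- **Certainty:** add risk, information and both earlier response groups, or the strata the coin actually uses.

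State the general rule that no response enters the model for a factor assigned before it. If effects given earlier responses are intended, define them here as well.

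The cost is wording plus 3 degrees of freedom for information and 4 for certainty, or up to 15 if all 2 × 2 × 2 × 2 = 16 histories are used as strata, out of 420 respondents. No new data are needed, because the platform needs these variables to allocate and stores the survey responses. Results says analysis starts only after the survey closes, so on the timeline described the change can precede it.

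### The stated regression adjusts for three demographics but leaves out the AI-attitude and AI-experience scores taken before randomisation, so precision is probably given up; there is no bias

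*Protocol article*

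**What the plan says.** The Statistical Analysis section of the protocol article specifies regression models with confidence as the outcome, in which the assignment indicator, "age, gender, and race are variables". A second sentence announces effects within subgroups formed from baseline variables, without naming those variables.

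The Overview lists the baseline questionnaires, which include "attitudes toward and experience with AI or machine learning (ML) in medicine", and continues: "They will then be randomly assigned to a 3-part" vignette. The AI items therefore precede the first randomisation. Survey Instruments gives their number: "7-10 questions assessing experience and 11 questions assessing attitudes".

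Hypotheses and Outcome Variables defines the primary outcomes as "ratings, on a Likert scale, of perceived confidence in the AI algorithm" and a matching 5-point rating of how effective its use was. Hypothesis 2 in the same section makes the effect of disclosure depend on the physician's earlier exposure to AI.

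**The concern.** A covariate improves a randomised comparison to the extent that it predicts the outcome. Here the outcomes are attitudes toward one AI tool, and the baseline battery measures attitudes toward, and experience with, medical AI in general. In content, these scores are the closest thing in the survey to a baseline value of the outcome. The stated model uses age, gender and race and leaves these scores out. Any between-physician variance that they would explain stays in the error term of the vignette effects.

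Precision is at stake, and respondents are hard to recruit. The Results section reports 35 complete responses from email, which leaves 420 - 35 = 385 to come by mail. The scores are already collected, so using them needs no further recruitment.

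**Working it through.** **The plan's own figure.** The Power Analysis gives 420 for at least 80% power at an effect size of 0.15, aimed at finding the best embedded regime. It does not report alpha, the number of regimes or their covariance, so the figure cannot be reproduced uniquely. With alpha 0.05 and SD 1 assumed:

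- A plain two-group comparison of 0.15 SD needs 698 per group, 1396 in all.
- A simulated comparison with the best regime gives anything from 55 to 2791 over 2-128 regimes and correlations of 0-0.9. Some settings come near 420 (8 regimes, correlation 0.7: 427; 32 regimes, correlation 0.8: 419).

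The 420 is neither confirmed nor refuted, and nothing below depends on how it was derived.

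**Inputs from the article.** N = 420; three factors with two levels each, so about 210 per level if balanced; model terms and baseline items as quoted above.

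**Inputs assumed.** Two-sided 5%, 80% power. r is the correlation of the baseline AI scores with the outcome, given age, gender and race. The article gives no value, so a range from zero is used.

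**Formulas.**

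- Detectable contrast under the stated model: (1.960 + 0.842) × sqrt(2/210) = 2.802 × 0.0976 = 0.273 SD, in units of the SD left after the stated covariates.
- Variance factor after adding the scores: 1 - r².
- Effective N: 420/(1 - r²).
- Detectable contrast: 0.273 × sqrt(1 - r²).
- Power of a contrast that has 80% under the stated model: Φ(2.802/sqrt(1 - r²) - 1.960).

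| r | Variance explained (r²) | Effective N | Detectable contrast (SD) | Power |
|---|---|---|---|---|
| 0 | 0% | 420 | 0.273 | 80% |
| 0.2 | 4% | 438 | 0.268 | 81.6% |
| 0.3 | 9% | 462 | 0.261 | 83.6% |
| 0.4 | 16% | 500 | 0.251 | 86.4% |
| 0.5 | 25% | 560 | 0.237 | 89.9% |
| 0.55 | 30% | 600 | 0.229 | 91.8% |

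The last power is Φ(2.802/0.837 - 1.960) = Φ(1.389).

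**Check on the Likert scale.** The outcome has five categories, so the gain was also simulated: 420 respondents, a 5-point outcome, a true shift of 0.3 SD on the underlying scale, and least squares with and without the score. The ratio of the effect's variance with the score to that without it was 0.97 at r = 0.2, 0.92 at r = 0.3, 0.86 at r = 0.4 and 0.77 at r = 0.5. These are close to 1 - r², so most of the gain survives the coarse scale. At r = 0 the ratio was 1.002, so a useless score costs almost nothing.

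**The case against.** The strongest reply is that the Statistical Analysis section is a two-sentence summary. It names one outcome where there are two, and one assignment indicator where there are three randomised factors, and it does not say that the covariate list is closed. A fuller plan may include the AI scores. Hypothesis 2 and the sentence on subgroup effects also suggest that baseline AI measures will be used somewhere. Leaving out a prognostic covariate does not make a randomised comparison wrong, and the gain rests on a correlation that nobody has reported.

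Part of this stands. The point concerns efficiency only, and its size is an assumption whose range must include zero. The relevant variance is what the scores add beyond age, gender and race. The Introduction says that inference on the final response draws on earlier factors and responses. Where later-stage models condition on those answers, the answers may already absorb part of the same variance.

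The rest does not remove the point. The article does name its covariates, so the choice is stated and not merely left open. The subgroup sentence names no variable and does not put the scores in the model. Hypothesis 2 shows that the authors expect exposure to matter, which favours including it.

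Three stronger readings are tempting and unsupported:

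- A reader might infer that the vignette effects are biased. They are not, because the factors are randomised.
- A reader might infer that the final sample will fall short of 420. Email recruitment was slow, but Survey Implementation and Results keep the survey open until the target is reached.
- A reader might infer that age, gender and race are unrelated to the outcome. The article gives no figure either way.

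**Conclusion.** The point holds as a modest matter of precision. The stated model omits the pre-randomisation measures closest in content to the primary outcomes.

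Under the assumption that they explain 0-30% of the variance left after the demographics, adding them is worth between nothing and 180 respondents (600 - 420). The detectable contrast then lies between 0.273 and 0.229 SD. At r = 0.2 the gain is only 4%, about 18 respondents; at r = 0.3 it is 9%, about 42. A reader might infer a gain of at least 10% for every factor, but no document supports a floor above zero or the same gain at every stage.

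The case for acting is that the possible gain is useful, the possible loss is close to nil and the data are already being collected. Adding the scores as covariates does not by itself test Hypothesis 2, which needs exposure to interact with the information factor; that is a separate matter.

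**What to change.** Before analysis starts, prespecify the baseline AI-attitude score and the baseline AI-experience score as continuous covariates in the primary models for both confidence and perceived effectiveness, alongside age, gender and race. State how each score is formed. The measures are described as adapted, and the number of experience items varies from 7 to 10, so the scoring rule and the handling of items not shown or not answered should be fixed in advance.

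The cost is about two degrees of freedom, a short scoring rule and a change of wording, with no new data. Timing matters because the Results section says that analysis begins as soon as the target is reached. Attitude scores added after the results are seen would look data-driven.
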